# Group schema therapy versus group cognitive behavioral therapy for social anxiety disorder with comorbid avoidant personality disorder: study protocol for a randomized controlled trial

**DOI:** 10.1186/s13063-016-1605-9

**Published:** 2016-10-08

**Keywords:** Social anxiety disorder, Randomized controlled trial, Group schema therapy, Group cognitive behavioral therapy, Avoidant personality disorder

## Abstract

**Background:**

Social anxiety disorder (SAD) with comorbid avoidant personality disorder (APD) has a high prevalence and is associated with serious psychosocial problems and high societal costs. When patients suffer from both SAD and APD, the Dutch multidisciplinary guidelines for personality disorders advise offering prolonged cognitive behavioral therapy (CBT). Recently there is increasing evidence for the effectiveness of schema therapy (ST) for personality disorders such as borderline personality disorder and cluster C personality disorders. Since ST addresses underlying personality characteristics and maladaptive coping strategies developed in childhood, this treatment might be particularly effective for patients with SAD and comorbid APD. To our knowledge, there are no studies comparing CBT with ST in this particular group of patients. This superiority trial aims at comparing the effectiveness of these treatments. As an additional goal, predictors and underlying mechanisms of change will be explored.

**Methods/design:**

The design of the study is a multicentre two-group randomized controlled trial (RCT) in which the treatment effect of group cognitive behavioral therapy (GCBT) will be compared to that of group schema therapy (GST) in a semi-open group format. A total of 128 patients aged 18–65 years old will be enrolled. Patients will receive 30 sessions of GCBT or GST during a period of approximately 9 months. Primary outcome measures are the Liebowitz Social Anxiety Scale Self-Report (LSAS-SR) for social anxiety disorder and the newly developed Avoidant Personality Disorder Severity Index (AVPDSI) for avoidant personality disorder. Secondary outcome measures are the MINI section SAD, the SCID-II section APD, the Schema Mode Inventory (SMI-2), the Inventory of Depressive Symptomatology Self-Report (IDS-SR), the World Health Organization Quality of Life-BREF (WHOQOL-BREF), the Difficulties in Emotion Regulation Scale (DERS), the Rosenberg Self-Esteem Scale (RSES) and the Acceptance and Action Questionnaire (AAQ-II). Data will be collected at the start, halfway and at the end of the treatment, followed by measurements at 3, 6 and 12 months post-treatment.

**Discussion:**

The trial will increase our knowledge on the effectiveness and applicability of both treatment modalities for patients suffering from both diagnoses.

**Trial registration:**

Dutch Trial Register: NTR3921. Registered on 25 March 2013.

**Electronic supplementary material:**

The online version of this article (doi:10.1186/s13063-016-1605-9) contains supplementary material, which is available to authorized users.

## Background

Beginning with the Diagnostic and Statistical Manual of Mental Disorders (DSM)-III [1] and continuing in DSM-IV [2], individuals whose fears are manifest in most social situations are assigned to the generalized subtype of social anxiety disorder (SAD), while individuals whose fears are more circumscribed are grouped together as a separate category, referred to as non-generalized social anxiety disorder. Since the introduction of the generalized subtype, there is a controversy about the differences with avoidant personality disorder (APD) [3]. While some researchers emphasize that APD is a serious form of generalized SAD [4, 5], a growing number of studies indicate that there is a qualitative difference between the two disorders. Shortcomings in establishing interpersonal relationships and severe feelings of inferiority are seen as cardinal features of APD [3, 6, 7].

To preserve continuity with clinical practice, the categorical diagnoses and criteria for personality disorders in the DSM-5 are kept the same. An alternative dimensional model is added in which, besides limitations in (inter)personal functioning, specific maladaptive traits pertaining to the dimensions of ‘detachment’ and ‘negative affectivity’ characterize persons with APD. Detachment is reflected in maladaptive traits such as withdrawal, anhedonia and intimacy avoidance, while anxiousness and worry in relation to social situations characterize these patients with respect to negative affectivity [8]. Furthermore, on the basis of empirical findings, it has been suggested that avoidance is a dominant coping strategy not only in social but also in non-social situations in APD [9–11].

APD is associated with high societal costs due to frequent use of somatic and mental health care, a high risk for developing other mental disorders and suboptimal professional functioning. Furthermore, patients report a low quality of life, and for family members, having a relative with a diagnosis of APD is often a considerable burden [12].

In clinical practice, there is no consensus about which treatment is indicated for patients with diagnoses of both SAD and APD. In the Netherlands the multidisciplinary guidelines recommend offering prolonged cognitive behavioral therapy (CBT) in the case of SAD with comorbid APD [13].

A small number of effectiveness studies have shown that CBT and pharmacological interventions are effective for patients with SAD and comorbid APD [14, 15]. Research among a sample of patients with social anxiety and patients with social anxiety and comorbid APD showed that APD was not predictive of CBT treatment outcome, and that several subjects who received a diagnosis of APD before treatment no longer met criteria for APD after treatment [16]. CBT in group format is approximately as effective as individual CBT [17].

Furthermore, there is growing evidence that schema therapy (ST) is an effective treatment for patients with APD [18, 19]. Research has shown that APD is associated with emotional neglect and abuse in the past [20, 21]. When the normal, healthy developmental needs of childhood are not met, maladaptive schemas develop. Activation of these schemas can trigger an emotional, cognitive and behavioral state, which in ST is called a ‘schema mode’ [22]. APD can be well conceptualized in terms of schema modes, with detached and avoidant protector modes as prominent coping modes, lonely child and abandoned/abused child mode as prominent child modes and punitive parent mode as prominent internalized parent mode [10, 23]. Within ST different techniques are applied, including experiential techniques such as imagery rescripting and mode role-plays, that explicitly address dysfunctional coping modes. A new development is group ST (GST), where specific methods and techniques are applied to use the group process in order to facilitate the process of change [22, 24].

Because of the promising results of ST, we designed a superiority trial with the primary objective of investigating the effectiveness of group schema therapy (GST) compared to prolonged group CBT (GCBT) for patients with social anxiety disorder (SAD) and comorbid avoidant personality disorder (APD). More specifically the following research question has been formulated: What is the effect of prolonged GCBT compared with GST for SAD with APD? Since people included in this trial will be diagnosed with both SAD and APD, improvements can be realized in two different domains: with respect to SAD symptoms and with respect to severity of APD traits. Therefore, the research question can be more explicitly formulated in the following questions: How do the effects of prolonged GCBT and GST compare for social anxiety disorder? and How do the effects of prolonged GCBT and GST compare for avoidant personality disorder?

Investigating predictors, moderators and mediators of treatment can add valuable knowledge to our understanding of for whom, under what conditions and how treatments work, thus generating valuable hypotheses for future research [25]. Therefore, this study will, as a secondary objective, look at possible predictors, moderators and mediators of changes on the primary outcome measures. As putative mediators, emotion regulation, self-esteem and schema mode manifestations will be repeatedly measured and associated with outcome. To detect possible predictors and moderators of treatment, the (differential) predictive value of different baseline measures for changes on the primary outcome measures will be explored.

## Methods/design

### Design

The design of the study will be a 30-session (on a weekly basis), two-group (GST, GCBT) randomized controlled clinical trial with repeated measurements at baseline (T0), mid-test (T1), post-test (T2) and at 3 months follow-up (T3), half-year follow-up (T4) and 1-year follow-up (T5). Assessment will include diagnostic interviews, symptom questionnaires and quality of life, self-esteem, schema-related and emotion regulation measures. See Fig. 1 (Flow chart of enrolment, intervention and assessments) and Additional file 1 (Standard Protocol Items: Recommendations for Interventional Trials (SPIRIT) flow diagram) for an overview of the study; the SPIRIT checklist is presented in Additional file 2. Diagnostic interviews are based on the DSM-IV classification system [2], since the DSM-5 [8] was not yet available during the developmental phase of this study and there was an absence of diagnostic instruments based on the DSM-5 at the start of the study.

**Fig. 1 Fig1:**
[figure not shown]
Flow chart of enrolment, intervention and assessments

After conclusion of the experimental part of the study (3 months after the last session of the treatment), patients will enter a naturalistic follow-up period in which they are allowed to seek help the way they would normally do when they feel in need for further treatment.

The study will be performed at two sites of PsyQ, a large ambulatory mental health organization in the Netherlands. Two departments of anxiety disorders of PsyQ will participate, one located in The Hague and the other in Rotterdam. Other departments, for instance, the departments of depression or personality disorders, in the regions of The Hague and Rotterdam will be informed of the study and will be asked to refer eligible patients. If necessary to guarantee a sufficient inclusion of eligible patients, more treatment centres will be approached for study participation.

### Population/sample size

Before the start of the randomized controlled trial (RCT), a chart review showed that both the PsyQ location of Rotterdam and the PsyQ location of The Hague have an annual patient flow of 40 patients with both SAD as well as a comorbid APD. This represents an overall yearly *N* of 80, of which it is expected that approximately 90 % (*N* = 72) will be included. This means that every year in each department 36 patients can be randomized over the two conditions. CBT and ST groups consist of a maximum of 9 patients.

We know that CBT has a large effect on SAD compared to waitlist and a small to moderate effect compared to placebo [15]. With respect to ST, in a randomized trial comparing ST, clarification therapy and treatment as usual (TAU), Bamelis et al. [19] found an odds ratio between ST and TAU in recovery from PD diagnosis in the 3–4 range (depending on the specific (sensitivity) analysis), which is equivalent to Cohen’s *d* = .60–.76 [26]. Though a substantial number of patients in the ST condition had a diagnosis of APD, only a small minority of patients received CBT as TAU. No studies are available directly comparing ST with CBT with respect to APD with comorbid SAD. We therefore designed our RCT as a superiority trial with enough statistical power to detect a difference in outcome between treatments (if present) with a medium effect size (Cohen’s *d* = .5). We chose this minimum difference because such a difference is important based on a patient’s perspective or clinical knowledge. Expecting larger differences in outcome does not seem realistic and might result in an underpowered study, while detecting smaller differences is of less relevance for clinical practice. Thus, we designed our study to detect a medium effect size (0.50) with a power of 80 % and a two-tailed alpha set at 0.05 on the primary outcome measures, severity of social anxiety (Liebowitz Social Anxiety Scale Self-Report, LSAS-SR) and severity of avoidant personality disorder (Avoidant Personality Disorder Severity Index, AVPDSI). This implies that 64 patients per study group and in total 128 patients are needed for the present project.

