### Statistical analysis

Pre-test differences between both treatment groups and between treatment completers and dropouts will be calculated by means of independent *t* tests, nonparametric tests or chi-square tests when appropriate. Multilevel analysis (MLA) will be used to investigate the effectiveness of GCBT and GST in reducing social anxiety symptoms and manifestations of AVPD, and the secondary outcomes. MLA is especially suitable to analyse repeated measure data because it takes into account the dependencies among observations nested within individuals. Another advantage of this methodology is its ability to handle missing data, a problem often occurring in longitudinal research [66]. The data has a three-level hierarchical (multilevel) structure: repeated measures at the first level, individuals at the second level, treatment condition at the third level. For dimensional outcomes the appropriate underlying distribution (e.g. normal, gamma, negative binomial) will be determined based on the observed distributions of residuals. For the repeated part, the best fitting covariance structure will be determined empirically. Moreover, multilevel logistic regression analysis will be performed in order to investigate whether GCBT compared to GST results in a higher proportion of remitted APD. Survival analysis will be used to compare conditions in treatment retention. The identification of possible predictors, moderators and mediators will be based upon the recommendations of Kraemer [25]. Linear regression methods will be applied to identify predictors/moderators related to treatment outcome. Bootstrapping methods [67] will be used to investigate the mediating effects of, for example, emotion regulation on symptom reduction. Furthermore, effect sizes and clinical significant change according to the Jacobson and Truax criteria [68] will be calculated to estimate respectively the magnitude of the treatment effect and the significance of the results for clinical practice.

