Both treatment protocols will be suitable for use in a clinical setting. The semi-open character of the groups, in which influx of patients is allowed every 10 weeks, diminishes waiting time and is therefore an ethical solution in case of long waiting lists as a consequence of lengthy treatments for patients with severe psychopathology. Also, from an organizational perspective, in which limitation of waiting time is considered important, this format can be attractive and might possibly even offer a cost-effective option for treatment of APD [13]. The semi-open character enables formation of groups with comparable psychiatric morbidity, allowing for contact with fellow patients. The size of the intended study sample will be sufficient to reliably detect differential treatment effects of a medium effect size or larger, and the relatively limited waiting time is expected to have a positive effect on the influx of patients. The selected measuring instruments are scientifically sound, and the repeated measurements allow for a close monitoring of changes in time, as well as mediation analyses of putative working mechanisms. The follow-up period of one year enables us to monitor how patients fare after the study treatment.

However, there are also some limitations to consider, given the chosen research design. The decision to compare GST with GCBT, *with GCBT as treatment as usual (TAU),* instead of a no-treatment or attention control condition might affect internal validity, since it sets boundaries on the possibility to control for other potentially influencing factors not directly related to the therapeutic context. When the effects of both treatments prove to be not significantly different, the absence of an inactive condition implies that one cannot exclude the possibility that factors such as passage of time or attention may have critically influenced outcomes observed. The influence of the factor time is, however, expected to be limited, since APD, like other personality disorders, is by definition assumed to be persistent [8], and recent studies show that APD symptoms are relatively stable over time [71, 82, 83]. Moreover, the addition of a control group would, in our opinion, have some serious ethical consequences, because it would deprive help-seeking patients of treatment for too long a period of time.

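### The 80% power claimed for 64 patients per arm has no allowance for therapy-group clustering or missing outcomes, so the calculation given does not support it unconditionally

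*Protocol article*

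**What the plan says.** Population/sample size in the protocol article sets out the target: "we designed our study to detect a medium effect size (0.50"), "with a power of 80" per cent and "a two-tailed alpha set at 0.05 on the primary outcome measures". It concludes: "This implies that 64 patients per study group and in total 128 patients are needed for the present project". The same section caps the therapy groups in both arms at 9 patients. The Abstract (Methods/design) makes the required number the enrolled number: "A total of 128 patients aged 18–65 years old will be enrolled".

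On missing data, Statistical analysis relies on the multilevel model: "Another advantage of this methodology is its ability to handle missing data, a problem often occurring in longitudinal research". It names three levels: repeated measures, individuals and treatment condition. Therapy group is not among them. The section on inclusion procedure and randomization provides for uneven dropout from treatment. Dropout and follow-up covers withdrawal and termination for missed sessions, and says that patients who leave treatment are still asked for follow-up assessments.

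The Discussion lists the sample size as a strength: "The size of the intended study sample will be sufficient to reliably detect differential treatment effects of a medium effect size or larger".

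**The concern.** The sample-size statement treats 128 patients as independent and completely observed. The rest of the article describes something else. Patients share a therapy group for 30 sessions. Schema therapy uses the group process as a means of change, and the cognitive behavioural arm relies partly on learning from other members. Outcomes of patients in the same group may therefore be correlated. Follow-up runs to a year after treatment, and missing data are described as common.

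A multilevel model can use incomplete records, but it does not restore the information that was lost. Within the stated calculation, any missing outcome and any positive within-group correlation lower power, and there is no margin to absorb either.

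What is at stake is how a non-significant result is read. The Discussion considers that case and locates the difficulty in the lack of an inactive control. It does not mention power. A reader who accepts the unconditional claim would give a null result more weight against d = 0.5 than the calculation warrants.

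**Working it through.** **Inputs from the article.** d = 0.5, two-sided alpha 0.05, 64 per arm, 128 enrolled, groups of at most 9, randomization in pairs (1:1).

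**Inputs assumed, because the article gives none.** Intraclass correlation (ICC) 0 to 0.10, outcome loss L of 0 to 20%, and correlation r = 0.5 between baseline and outcome.

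**1. Reproduce the stated number.** The noncentrality is d × √(n/2) = 0.5 × √32 = 2.83 on 126 degrees of freedom (df). Noncentral-t power is 80.1% at 64 per arm and 79.5% at 63. So 64 is the smallest n that reaches 80%, and the arithmetic is right.

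**2. Loss only.** n = 64(1 − L).
- L = 10%: n = 57.6, power 75.8%.
- L = 20%: n = 51.2, power 70.7%.

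**3. Clustering only, groups of m = 9.** Design effect DE = 1 + (m − 1) × ICC, and n = 64/DE.
- ICC 0.02: DE = 1.16, n = 55.2, power 74.0%.
- ICC 0.05: DE = 1.40, n = 45.7, power 65.7%.
- ICC 0.10: DE = 1.80, n = 35.6, power 54.7%.

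**4. Both.** Loss also shrinks the observed group, so m = 9(1 − L).
- ICC 0.05, L = 20%: m = 7.2, DE = 1 + 6.2 × 0.05 = 1.31, n = 51.2/1.31 = 39.1, power 58.8%. The d detectable with 80% power is about 0.64.
- ICC 0.02, L = 10%: m = 8.1, DE = 1.142, n = 57.6/1.142 = 50.4, power 70.1%.

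**5. Credit for baseline adjustment.** Divide the effective n by 1 − r² = 0.75. This supposes that baseline explains the same share of variance between and within groups. The last column uses cluster df: 64/9 is about 7 groups per arm, so 14 − 2 = 12 df.

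| ICC | Loss | Effective n, unadjusted | Power, unadjusted | Effective n, r = 0.5 | Power, r = 0.5, patient-level df | Power, r = 0.5, 12 df |
|---|---|---|---|---|---|---|
| 0 | 20% | 51.2 | 71% | 68.3 | 83% | not applicable |
| 0.02 | 10% | 50.4 | 70% | 67.3 | 82% | 76% |
| 0.05 | 0% | 45.7 | 66% | 61.0 | 78% | 72% |
| 0.05 | 20% | 39.1 | 59% | 52.1 | 72% | 65% |

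The unadjusted figure in the last row is 53% on 12 df.

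**6. If therapy group is left out of the model, as the stated levels suggest.** At ICC 0.05, m = 9 and complete data, the standard error is too small by a factor √1.40 = 1.183. By the normal approximation, the two-sided type I error is P(|Z| > 1.96/1.183 = 1.66), about 10%. The chance of rejection at d = 0.5 is P(Z > (1.96 − 2.83)/1.183 = −0.73), about 77%. The damage then falls mainly on the error rate and less on apparent power.

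**The case against.** Four points on the other side have weight.

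First, nothing is miscalculated, and a journal article need not print every sample-size assumption. That is so. But the point concerns two printed claims, in Population/sample size and in the Discussion, which carry no condition. It does not rest on a missing detail.

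Second, the planned analysis uses repeated measures: the LSAS-SR at six occasions and the AVPDSI at three. It may recover much of the loss. This stands, and it limits what can be said. A reader might infer that the trial simply lacks 80% power, or has only a 55 to 70% chance of detecting d = 0.5. The documents do not support that. They give no ICC, loss rate or baseline correlation, and at r = 0.5 power reaches 80% or more in two of the four tabulated cases on patient-level df. Equally, the sample-size section invokes no such gain, so it cannot be used to justify the 80% stated there.

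Third, treatment dropout is not outcome loss. Patients who leave treatment are asked for follow-up data, so outcome loss may well be smaller than dropout. That request reduces loss but does not guarantee complete data.

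Fourth, the clustering losses in steps 3 to 5 presuppose an analysis that accounts for therapy group, which the stated model does not. Step 6 shows what happens instead, and the model therefore has to be part of the remedy.

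A reader might also treat each semi-open group as one large cluster for the whole trial, which would make the loss far bigger. The cap of 9, with 30 sessions and entry every 10 weeks, means that patients far apart in time never meet, so one common correlation across them is unsupported. The same overlap makes the fixed-group design effect used here an approximation.

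**Conclusion.** The concern holds as a statement about the calculation. Sixty-four per arm is the exact minimum for independent, complete data. Enrolment equals that number, and the article itself describes group delivery and expects missing data. The unconditional 80% and the Discussion's sufficiency sentence are not supported by what is given.

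The direction is certain for that calculation. The size is not known and depends on assumed inputs: from about 76% (10% loss, no clustering) to 55% (ICC 0.10, complete data) when one factor acts alone, and 59% at ICC 0.05 with 20% loss. Baseline adjustment at r = 0.5 moves the tabulated cases to between 72% and 83% on patient-level df, and lower on cluster df where groups are clustered. This should be fixed, but it does not show that the trial is too small.

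**What to change.** Keep 128 patients.

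- **Population/sample size:** state that 80% power at d = 0.5 applies to independent patients with complete data and no baseline adjustment. Add a table of power and detectable d over assumed ICC 0 to 0.10, groups of up to 9 and outcome loss of 0 to 25%, with and without baseline adjustment. Compute it under a model that includes therapy group, and say which degrees of freedom are used. Note that treatment dropouts are asked for follow-up data, so the loss rate refers to missing outcomes and not to treatment dropout.
- **Statistical analysis:** add therapy group to the stated levels, since leaving it out makes the standard errors too small.
- **Discussion:** replace the sufficiency sentence with the range from the table.

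The cost is wording, a short calculation and one added model term. No patients, visits or measurements are added. The stated power becomes conditional and, in some scenarios, less favourable.
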